#### UPAL gel (dMD-001) implantation

2.5.2

UPAL gel (dMD-001) is manufactured by quality management system and is provided by Mochida Pharma Co. Ltd (Mochida Pharma Co. Ltd., Tokyo, Japan). Following standard discectomy, the treating surgeon will evaluate the feasibility of AF re-approximation. If the evaluation is positive, a board-certified orthopaedic specialist will inject the UPAL gel into the IVD. Specifically, up to 2 mL of UPAL solution will be delivered into the IVD defect using a syringe, and 10 mL of 0.1 mol/L CaCl_2_ solution will then be applied to the surface of the UPAL solution to gelate the alginate. At 5 min after application of CaCl_2_ solution, the surgical site will be irrigated with a full-dose of sterile, clinical-grade, normal saline. All patients will receive standard postoperative care will be implemented. Braces after surgery will not be used.

Stopping criteria during UPAL gel implantation.i.The volume of UPAL solution delivered into the IVD defect exceeds 2.0 mL.ii.The UPAL solution does not gelate upon treatment with CaCl_2_.iii.Any other reason judged by the treating surgeon to render the participant unsuitable for the trial at this time such as an allergic reaction.

If either of the above terminating criteria is met, the surgical site will be irrigated with a full-dose of sterile, clinical-grade, normal saline. Assessment of safety after injection of the UPAL solution will be performed for up to 24 weeks. The reason for stopping the UPAL gel implantation will be recorded.

### Measures

2.6

#### Primary outcome measurement

2.6.1

The primary outcomes of this trial are the feasibility and safety of the procedure. Feasibility is defined based on the quality-control release criteria for the clinical use of UPAL as a biomaterial, which refer to the suitability of the biomaterial for intraoperative manipulation and implantation into the IVD defect [13]. Safety is defined in terms of the incidence of serious adverse events and serious adverse reactions, according to the Pharmaceutical and Medical Device Act currently in effect in Japan [13]. Any adverse events, either local (e.g., infection, haematoma) or systemic (e.g., fever, allergic reaction), will be handled according to the Japanese guidelines for Good Clinical Practice. The following serious adverse events will be recorded [1]:i.Abdominal painii.Back painiii.Back and leg painiv.Cancerv.Deathvi.Dural tearvii.Heat attack/cardiac arrestviii.Haematoma/seromaix.Hip painx.Leg painxi.Neck/cervical painxii.Pneumonia/atelectasisxiii.Spinal fluid leakxiv.Wound infectionxv.Local or systemic feverxvi.Abnormal blood coagulationxvii.Recurrence of herniation

Recurrent herniation is defined as re-herniation at the same vertebral level. A group of non-investigator physicians will independently adjudicate the primary cause for any secondary surgery involving the same vertebral level. Re-herniation will be considered recurrent if all extruded NP material is removed during the initial surgery and a new offending fragment, including the gel, is identified, or if there is evidence that not all extruded NP material had been removed during the initial surgery and residual material remains [1].

#### Secondary outcome measurement

2.6.2

The secondary outcomes of this trial are: (i) physical function scores; (ii) self-reported patient satisfaction at 1 day before surgery (baseline) and at 1, 4, 12, and 24 weeks after surgery; and (iii) morphological and compositional quality of the IVD tissue evaluated on MRI before surgery (baseline) and at 24 weeks after surgery.

#### Physical examination to evaluate physical function

2.6.3

The finger-to-floor distance will be measured as the shortest distance (in cm) between the floor and fingertips as the patient stands and bends down from the waist with arms stretched, without bending the knees [14,15]. The straight-leg-raising test will be conducted to measure the maximum angle (in degrees) between a horizontal surface and the lower extremity as the patient raises the leg by flexing the hip, with the knee passively extended [14]. The range of motion of the lumbar spine will be measured using the Modified Schober's test; specifically, three marks (one at the lumbosacral junction, one at the spinous process lying 10 cm above the first mark, and one at the spinous process lying 5 cm below the first mark) will be made with the patient in the standing position, and the range of motion will be measured as the distance (in cm) between the inferior and superior marks at full hip extension minus the distance at full hip flexion [16]. The Japanese Orthopaedic Association (JOA) score will be used to evaluate functional status and the severity of clinical symptoms associated with lumbar disc herniation; the JOA score ranges from 0 to 29, with higher scores indicating better functional status [16].

#### Self-reported questionnaires for evaluating pain and health-related quality of life

2.6.4

A 100-point VAS (0–100 mm, with higher scores representing worse pain) will be used to assess leg pain on both the worst-affected and least-affected side, as well as back pain. The preoperative VAS score for the worst-affected leg will be considered as the reference for postoperative comparisons [1]. Health-related quality of life will be assessed using the 36-item Short Form Health Survey (0–100, with higher scores representing better quality of life) [17]. Overall functional outcome will be assessed using the Oswestry Disability Index (0–100, with higher scores indicating more severe pain-related disability) [18]. Low-back pain-specific quality of life will be evaluated using the Roland-Morris disability questionnaire (0–24, with higher scores representing worse quality of life) [19]. Multidimensional evaluation of health status, including dysfunctions, disabilities, and psychosocial problems associated with the lumbar spine disorder will be assessed using the JOA Back Pain Evaluation Questionnaire (0–100, with higher scores representing better health status) [20]. The use of medication during the week preceding each follow-up visit will be recorded at 1, 4, 12, and 24 weeks postoperatively. Medication intake is considered a useful surrogate for outcome measures such as pain and may represent a confounding factor or cointervention [12].

#### MRI protocol for evaluating the IVD tissue

2.6.5

MRI scans obtained at enrolment and 24 weeks postoperatively will be assessed by a trained investigator. All MRI examinations will be performed with a 3.0-T scanner. First, sagittal conventional T2-weighted images will be obtained using a turbo spin-echo sequence. Next, sagittal T1ρ-, T2*-, and diffusion-weighted images will be obtained using a 3D gradient-echo or an echo planar-imaging pulse sequence [[21], [22], [23]].

For each participant, two board-certified orthopaedic specialists with over 10 years of experience will independently assess the treated lumbar IVD on mid-sagittal T2-weighted images according to the Pfirrmann grading system [24], as described below:i.Grade I - homogeneous shape, bright hyperintense (white), normal IVD height, clearly distinguishable AF and NP.ii.Grade II - nonhomogeneous shape with or without horizontal grey bands, hyperintense (white) signal, normal IVD height, clearly distinguishable AF and NP.iii.Grade III - nonhomogeneous shape, intermediate (grey) signal intensity, normal or slightly decreased IVD height, AF and NP not clearly distinguishable.iv.Grade IV - nonhomogeneous shape, hypointense (dark grey) signal, normal to moderate decrease in IVD height, completely indistinguishable AF and NP.v.Grade V - similar to grade IV, but with collapsed IVD space.

The intervertebral disc height index will be obtained as the ratio between the IVD height and the proximal vertebral body height, both measured for the middle portion, on mid-sagittal T2-weighted images [25,26].

After Pfirrmann grading of IVD degeneration is carried out based on mid-sagittal T2-weighted images, T1ρ, T2* and apparent diffusion coefficient values of NP and AF will be assessed. The 3D gradient-echo images with different spin lock and echo times will be fitted on a pixel-by-pixel basis to generate a T1ρ and T2* relaxation time maps, respectively [21]. Regions of interest involving the NP, anterior AF, and posterior AF will be set manually on the T1ρ and T2* maps with reference to the T2 images. The values obtained for the anterior and posterior AF will be averaged to determine a single value representative of the AF [21]. The T1ρ, T2*, and apparent diffusion coefficient values of the NP and AF will be assessed as secondary outcomes. All measurements will be performed twice by a single observer at an interval of 4 weeks.

### Sample size

2.7

This is a first-in-human pilot study designed to generate data that can be used to inform a future large randomised controlled trial should the intervention appear feasible and safe, and show trends of effectiveness. To date, no data has been published on the quantitative interactions of a biomaterial with the IVD tissue and how such interactions might affect the IVD space after discectomy. Therefore, we could not conduct a priori sample size calculations for this pilot study because the effect size cannot be estimated at this time. The study aims to recruit 40 participants [12] because we expect that such a sample size will be achieved within a reasonable time based on the study recruitment rates within our community. Moreover, a sample size of 40 participants is considered sufficient for an exploratory clinical trial because it allows to detect with 95% probability differences in one or more adverse events that exhibit an incidence ratio of 7.5%. We aim to evaluate key trial parameters such as preliminary indications of effectiveness and to advise of our calculation of a sample size for powering a full trial in the future [27]. Published guidelines recommend that pilot studies be undertaken to allow trial protocols to be tested under study conditions prior to evaluation in a full randomised controlled trial [12,28]. Thus, the results of this limited phase II trial will also assist in determining the relevance and possible benefits of performing a significantly larger phase III randomised controlled trial [12].

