## Abstract

Herniated nucleus pulposus (NP), one of the most common diseases of the spine, is surgically treated by removing the sequestered NP. However, intervertebral disc (IVD) defects may remain after discectomy, leading to inadequate tissue healing and predisposing patients to IVD degeneration. An acellular, bioresorbable, ultra-purified alginate (UPAL) gel (dMD-001) implantation system can be used to fill any IVD defects in order to prevent IVD degeneration after discectomy. This first-in-human pilot study aims to determine the feasibility, safety, and perceived patient response to a combined treatment involving discectomy and UPAL gel implantation for herniated NP. We designed a one-arm, double-centre, open-label, pilot trial. The study started in November 2018 and will run until a sample of 40 suitable participants is established. Patients aged 20–49 years, diagnosed with isolated lumbar IVD herniation and scheduled for discectomy represent suitable candidates. All eligible participants who provide informed consent undergo standard discectomy followed by UPAL gel implantation. The primary outcomes of the trial will be the feasibility and safety of the procedure. Secondary outcomes will include self-assessed clinical scores and magnetic resonance imaging-based measures of morphological and compositional quality of the IVD tissue. Initial outcomes will be published at 24 weeks. Analysis of feasibility and safety will be performed using descriptive statistics. Both intention-to-treat and per-protocol analyses of treatment trends of effectiveness will be conducted.

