### Trial design

2.2

This first-in-human study is being conducted as a double-centre, open-label, pilot trial. An overview of the process of the trial is presented in Fig. 1 and Table 1. Protocol is version 1.0 and the protocol was fixed on July 5, 2018. The study started in November 2018 and recruitment of patients will end in September 2020 or will run until a sample of 40 suitable participants is established. And the last patient has been recruited in September 2020.

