#### Discectomy

2.5.1

All participants will undergo macroscopic discectomy for lumbar IVD herniation. These open procedures will be conducted using standard or tubular retractors, with or without the use of an operating microscope or loupes [1]. Manual, nonautomated methods for herniated IVD removal will be used exclusively, and no percutaneous methods will be applied [1]. To standardize the fenestration site for UPAL gel implantation, the procedures will involve an AF incision of 5 mm × 5 mm using a no. 15 surgical scalpel blade. In patients with transligamentous extrusion-type or sequestration-type herniated disc, the AF opening will be measured and reported. After the AF incision, we aim to remove as much disc material as possible. It will not be a limited discectomy. The technique used for discectomy will be at the discretion of the treating surgeon [1]. Whilst the surgeons’ preference and skill may confound the outcomes, this represents an acceptable limitation that has been purposefully allowed in order to facilitate recruitment of participants from across a wider orthopaedic community [12].

Stopping criteria before UPAL gel implantation.i.The AF incision for discectomy exceeds 5 mm × 5 mm (i.e., the diameter of the incision exceeds 5 mm).ii.The treating surgeon judges that AF re-approximation is not feasible or there is some other reason rendering the patient unsuitable for UPAL gel implantation such as a spinal fluid leak due to an incidental tear of the dura mater.iii.The volume of sterile, clinical-grade, normal saline delivered into the IVD defect exceeds 2.0 mL, indicating rupture of the AF.

If either of the above criteria for termination is met, no UPAL gel implantation will be conducted after the standard discectomy, and the patient will be excluded from the trial. The reason for stopping the UPAL gel implantation will be recorded.

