### Statistical analysis

2.9

Statistical analyses will be conducted using SPSS version 22 (IBM Corp., Armonk, NY, USA). Data will be expressed as mean number ± standard deviation and frequency (percentage), as appropriate. Clinical scores and radiologic properties of the IVD at different time points during follow-up will be assessed using the paired *t*-test or Wilcoxon signed rank test, according to the normality of the population, which will be determined using D'Agostino-Pearson omnibus tests [13]. A two-tailed probability level of 0.05 will be considered significant. Continuous data will be analysed using linear mixed models, as such models are robust in longitudinal data analysis and account for correlations associated with repeated measurements [12]. As recommended by the revised Consolidated Standards of Reporting Trials statement, the mixed models will adjust for the baseline score of the outcome of interest [12,29]. Original data will be analysed using the Mann-Whitney *U* test. The risk ratio, risk difference, and number needed to treat will be calculated, together with 95% confidence intervals [12,29,30]. Statistical significance will be determined by χ^2^ analysis.

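### The 95% figure behind n = 40 is the chance of seeing at least one adverse event with a true incidence of 7.5%, not of detecting a difference or ratio, and section 2.7 should say so

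*Protocol article*

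**What the plan says.** Section 2.7 (Sample size) first says that no formal calculation was possible: "we could not conduct a priori sample size calculations for this pilot study because the effect size cannot be estimated at this time". It then sets the target, "The study aims to recruit 40 participants", and gives expected recruitment as the first reason. The second reason, and the only quantitative one, is that "it allows to detect with 95% probability differences in one or more adverse events that exhibit an incidence ratio of 7.5" per cent.

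Other parts of the article bear on how that sentence can be read:

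- **Design.** The abstract says "We designed a one-arm, double-centre, open-label, pilot trial".
- **Safety analysis.** Section 2.8 has safety summarised descriptively, as the rate of adverse events and reactions.
- **Comparator.** The Discussion places a discectomy-only historical control in a separate observational study, to follow this trial.
- **End of recruitment.** The abstract says "The study started in November 2018 and will run until a sample of 40 suitable participants is established". Section 2.2 says "recruitment of patients will end in September 2020 or will run until a sample of 40 suitable participants is established", and adds that the last patient was recruited in September 2020.

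**The concern.** Detecting a difference requires something to differ from: a concurrent arm, or a stated reference rate with a test against it. The article provides neither for adverse events. An incidence ratio likewise needs two incidences, and the 7.5% is a single one. As worded, the sentence therefore describes a property that this design does not have.

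Safety is a primary outcome of a first-in-human study whose results are meant to inform a larger randomised trial. Section 2.9 also lists risk ratio, risk difference, number needed to treat and a chi-square analysis. Next to that list, a reader could take section 2.7 to promise 95% power to find an excess of adverse events over discectomy alone. Several of the listed events, such as back pain, leg pain, dural tear and recurrent herniation, can follow discectomy itself. One occurrence among 40 patients would say nothing about an excess due to the gel.

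**Working it through.** **Inputs.** n = 40, probability 95% and incidence 7.5%, all from section 2.7. One arm, from the abstract. No reference rate is stated anywhere. Section 2.9 sets a general significance level ("A two-tailed probability level of 0.05 will be considered significant"), but nothing links it to the adverse-event sentence.

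**Step 1: reproduce the stated figure.** For an event with true incidence p in n independent patients, P(at least one) = 1 - (1 - p)^n. With p = 0.075 and n = 40, this is 1 - 0.925^40 = 1 - 0.0442 = 0.9558, or 95.6%. The stated 95% is reproduced. The rule of three gives the same pairing: 3/40 = 7.5%.

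**Step 2: invert it.** The smallest n giving 95% is ln(0.05)/ln(0.925) = 38.4, so 39 patients. The lowest incidence that 40 patients would show at least once with 95% probability is 1 - 0.05^(1/40) = 0.0722, or 7.2%. The same number is the one-sided 95% upper limit if none of the 40 has the event.

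**Step 3: try the sentence as worded.** The power to detect a difference needs a second rate and a test rule. The article gives no second rate and plans a descriptive safety analysis, so this power cannot be calculated from the document. The three stated numbers fit together without further input only as in Step 1.

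**Step 4: sensitivity to the number injected.** The sizes below 40 are illustrative; the article does not report any of them.

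| Patients injected | P(at least one event at 7.5%) | Upper limit if none seen (one-sided 95%) |
|---|---|---|
| 40 | 95.6% | 7.2% |
| 39 | 95.2% | 7.4% |
| 38 | 94.8% | 7.6% |
| 36 | 94.0% | 8.0% |
| 30 | 90.4% | 9.5% |

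**The case against.** The strongest reply is that this is loose English around a correct number. The sentence contains the words for one or more adverse events, which point to the at-least-one-event meaning. The section says that no formal calculation was made, calls the study an exploratory pilot, and gives recruitment as its first reason for 40. A reader of the whole article would see that safety is descriptive and that the discectomy-only comparison comes later. Much of this stands: the arithmetic is right, and no planned number changes. It does not rescue the terms for difference and ratio, which are affirmative statements in the only quantitative justification and have no referent in the trial.

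Three stronger readings are tempting, and the documents support none of them.

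- **That one arm cannot support the 95% at all.** One arm fully supports the probability of seeing at least one event. Only the wording about a difference or ratio is unsupported.
- **That patients stopped before the gel erode the 40.** Section 2.5.1 says of them that "the patient will be excluded from the trial". But section 2.3 places official enrolment at the surgeon's decision, after discectomy, to implant. Patients stopped before the gel therefore need not use up any of the 40 places.
- **That recruitment fell short.** Section 2.2 allows recruitment to end on a date, but nothing shows that 40 was missed, and a protocol article need not report the final count. A small shortfall would also matter little, as Step 4 shows.

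**Conclusion.** The point holds as an error in what the figure is said to mean. The 95%, 7.5% and 40 agree with one another as the probability of observing at least one occurrence of a given event (95.6%), and they say nothing about detecting a difference or a ratio. The calculation assumes independent patients with a common incidence, each counted once for the event type in question, and 40 patients injected and followed for safety. It applies to each event type taken singly.

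A reader might go further and conclude that the trial is too small or that its safety analysis is invalid. The documents do not support that: the study is a descriptive pilot, and 40 patients deliver the property that the numbers express.

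The recruitment wording is secondary. Section 2.2 gives a date or a count and the abstract gives only the count, so the article does not fix whether n = 40 is guaranteed. This affects the figure only if fewer than 39 patients are injected.

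**What to change.** Replace the sentence in section 2.7 with wording such as:

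> *With 40 patients injected there is a 95.6% probability of observing at least one occurrence of an adverse event whose true incidence is 7.5%; if none is seen, the one-sided 95% upper limit is 7.2%. The trial cannot detect a difference from discectomy alone.*

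Align the abstract with section 2.2 on whether the date or the count of 40 ends recruitment. If fewer than 39 patients were injected, recompute both figures for the actual number, using 1 - 0.925^n and 1 - 0.05^(1/n).

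The cost is a few sentences. No patients, assessments or analyses are added. The stated property becomes more modest, but it is one that the design delivers.

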### Feasibility and safety analysis

2.8

Data regarding feasibility and safety will be analysed using descriptive statistics [27]. The percentage of participants who (i) meet the inclusion criteria, (ii) agree to participate in this study, (iii) complete the intervention, and (iv) attend the follow-up assessment will be calculated. Feasibility will be described in terms of the (i) number of follow-up sessions attended by each participant, (ii) number of drop-outs, and (iii) proportion of participants recruited from the total number screened [27]. Additionally, feasibility will be evaluated as the rate of completion of UPAL gel implantation, which will be judged according to the adequacy of gelation of the surface of the injected UPAL solution after application of CaCl_2_ solution. The rate of completion of UPAL gel implantation will be assessed as the number of patients with adequate gelation divided by the number of patients who undergo discectomy followed by UPAL solution injection. Safety will be assessed as the rate of adverse events and reactions.

